### Comorbid conditions and adverse events

PHCPs and the research assistant will not monitor comorbid conditions regularly at exercise program sessions. The patient will continue their normal contact with their general practitioner and other healthcare professionals.

#### Adverse events

Adverse events are defined as any undesirable experience occurring during the study (regardless of whether this was related to the treatment) by the participant [49] and will be reported by both the participant and PHCP. Classification of adverse event severity is shown in Table 5. The PHCP will have a current first aid certificate and will record any adverse events that happen during the feasibility study period (8 weeks). Adverse events or discomfort experienced by participants during this study may relate to possible side effects from performing the exercise program. Participation in the exercise program may exacerbate individual comorbid condition(s), and some participants may also be at risk of falling. During the administration of the exercise program, should a severe exacerbation of a comorbid condition arise, an ambulance will be called, and the event will be documented in the patient’s file. There is also the possibility of uncovering an unexpected medical condition during the diagnostic phase of the exercise program. Should this arise, the participant will be referred to their general practitioner by the PHCP with a letter stating the relevant findings. In both cases, continuation in the study will be at the discretion of the participant and/or the participant’s general practitioner.

**Table 5 Tab5:** Classification of adverse event severity

*Mild*: asymptomatic or mild symptom, requiring self-care only (e.g. ice/heat, over-the-counter analgesic)	
*Moderate*: limiting age-appropriate activities of daily living (e.g. work, school) OR sought care from a medical doctor	
*Serious*: results in death OR is a life-threatening AE OR an AE resulting in inpatient hospitalization or prolongation of existing hospitalization for more than 24 h, a persistent or significant incapacity or substantial disruption of the ability to conduct normal life functions, a congenital anomaly/birth defect	

Changes in low back pain will be reported by participants via a daily SMS asking for a numerical ratings scale score (0–10) on the severity of their low back pain throughout the 8-week exercise program. If SMS data identifies an increase in low back pain, participants will be contacted to be asked whether they felt the exercise program may have caused an increase in low back pain. Additionally, the daily SMS will ask about any undesirable experiences related to the exercise program. If the SMS identifies an exacerbation of a comorbidity, the participant will be contacted to be asked about the nature of the adverse event.

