	Improvements in low back pain and function found clinically relevant by at least 50% of the participants	Improvements in low back pain and function found clinically relevant by at least 25% of the participants	Improvements in low back pain and function found clinically relevant by less than 25% of the participants
	Improvements in quality of life and illness burden by at least 50% of the participants	Improvements in quality of life and illness burden by at least 25% of the participants	Improvements in quality of life and illness burden by less than 25% of the participants
	No serious study-related adverse events during the study period	Less than five serious study-related adverse events during the study period	Five or more serious study-related adverse events during the study period

Green (go), where there are no concerning issues that threaten the success of the trial; amber (amend), where there are remediable issues, thereafter proceeding with caution; red (stop), when there are intractable issues that cannot be remedied

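### The daily SMS asks only about experiences related to the exercise programme, which is narrower than the protocol's own definition of an adverse event and likely to under-collect events

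*Protocol article*

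**What the plan says.** All four of the following statements are in the Adverse events section of the protocol article.

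- **Definition.** An adverse event is "any undesirable experience occurring during the study (regardless of whether this was related to the treatment) by the participant". Such events "will be reported by both the participant and PHCP".
- **Daily SMS, pain item.** A 0–10 back pain score is requested every day of the 8-week programme. If it rises, "participants will be contacted to be asked whether they felt the exercise program may have caused an increase in low back pain".
- **Daily SMS, adverse event item.** Here "the daily SMS will ask about any undesirable experiences related to the exercise program".
- **SMS follow-up.** "If the SMS identifies an exacerbation of a comorbidity, the participant will be contacted to be asked about the nature of the adverse event".

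Table 2 (Participants section) scores safety on serious study-related events only. Green requires "No serious study-related adverse events during the study period", amber is fewer than five, and red is five or more. The aims at the end of the Background include reporting adverse events. The section Comorbid conditions and adverse events says that comorbid conditions are not regularly monitored at the exercise sessions.

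**The concern.** The definition separates the occurrence of an event from its cause. The SMS adverse event item joins them again by making the participant decide on cause before reporting anything.

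This population makes that decision difficult. Everyone is 65 or older and has at least one target comorbidity with an illness burden score of 3 or above (Table 1). The protocol itself warns that exercise may worsen a comorbid condition and that some participants may be at risk of falling. The foreseeable harms are thus of a kind that a participant could easily ascribe to an illness they already have.

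At stake is the completeness of the adverse event record, and also the safety follow-up call, which depends on the SMS identifying the problem.

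**Working it through.** No figure in the plan bears on this point, so the check compares the wording of each collection route and then traces events through them.

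**Step 1. Routes by which an event can reach the record**

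| Route | Where stated | Frequency | Limited to programme-related? |
|---|---|---|---|
| SMS adverse event item | Adverse events | Daily, 8 weeks | Yes |
| SMS pain score | Adverse events | Daily, 8 weeks | No, but covers back pain only |
| PHCP record of any adverse event | Adverse events | 8 weeks; two supervised sessions a week (Intervention phase) | No |
| Scheduled adverse event collection | Table 4; in-person visits (Data collection) | 4 and 8 weeks | No limit stated |
| Call after a missed session | Patient recruitment, retention, and intervention adherence | When a session is missed | No, but asks for the reason for absence |

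**Step 2. The SMS item against the text around it**

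The definition includes events whatever their relation to treatment; the SMS item includes only those related to the programme. The item is therefore a strict subset of the definition. The following sentence expects the SMS to identify a comorbidity exacerbation. Apart from the pain score, the programme-related item is the only SMS content described, so an exacerbation can surface only if the participant already links it to exercise.

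The pain item does not share this fault. The score is taken first, without condition, and the question about cause comes after the increase has been seen.

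**Step 3. Four events traced through the routes**

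1. *Worse back pain.* The pain score picks it up whatever the participant believes about its cause.
2. *A non-serious worsening of a comorbidity at home, ascribed to the existing illness.* The truthful SMS answer is no, and no call follows. The event is recorded only if it comes up at a session or is recalled at 4 or 8 weeks. It does not enter the Table 2 safety row, but it is an adverse event under the definition.
3. *A serious event truly unrelated to the study.* The SMS may miss it. The safety row is unchanged because it counts related events only.
4. *A serious, truly related event ascribed to existing illness.* The SMS may miss it. The row is wrong only if every other route misses it too.

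**Step 4. Direction and possible size for the fourth case**

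Missing an event can only lower the count, so the error runs towards green: one true event counted as none turns amber into green, and five counted as four turns red into amber.

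As an illustration, let *c* be the probability that a truly related serious event is captured by at least one route and then judged correctly. Assume events are captured independently. The documents give no value for *c*; the range below is an assumption.

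- One true event, scored green: 1 − c.
- Two true events, scored green: (1 − c)².
- Five true events, still scored red: c⁵.

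| c | One event, green | Two events, green | Five events, red |
|---|---|---|---|
| 0.90 | 0.10 | 0.01 | 0.59 |
| 0.75 | 0.25 | 0.06 | 0.24 |
| 0.50 | 0.50 | 0.25 | 0.03 |

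Here *c* covers all routes together. The routes without a relatedness limit raise it above what the SMS alone would give, so the table does not estimate the effect of the SMS wording.

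**The case against.** The strongest objection is that the SMS is not the gate to the safety record. The PHCP "will record any adverse events that happen during the feasibility study period (8 weeks"), Table 4 collects adverse events at two visits, and a missed session prompts a call. Serious events under Table 5 include death, life-threatening events, hospitalisation and significant incapacity; with two supervised sessions a week, many would cause an absence and hence a recorded reason. This stands. A reader might infer from the SMS wording that events are filtered by self-attribution before the safety row is scored, and that the row is biased towards green. The documents do not support that: other routes are unfiltered, and the row excludes unrelated events by design.

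Two figures may tempt a reader to put a size on such a bias. With no events in 24 participants, the upper 95% limit is 1 − 0.05^(1/24) = 11.7% one-sided, or 1 − 0.025^(1/24) = 14.2% from a two-sided interval. The SMS goes out up to 24 × 56 = 1,344 times. The first would be the same under any wording of the SMS, and the second counts messages. Neither measures missed events.

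A second objection is that the article paraphrases the SMS and the message itself is not shown. The expectation that it reveals comorbidity exacerbations may mean that the real text is broader. That is possible, and it limits certainty about what participants will read. It does not remove the mismatch between the two statements as published.

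Third, a reader might infer that events during the baseline tests go unrecorded, since Table 4 has no baseline adverse event entry and the recording period is given as 8 weeks. The text is ambiguous here: the definition covers the whole study, and a PHCP carries out the baseline examination. Nor is it a finding that the article names no assessor of relatedness, a detail commonly left to the full protocol.

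What the objections leave standing is case 2 in the working. The unfiltered routes are less frequent, the scheduled visits are four weeks apart and rely partly on recall, and participants who withdraw may miss them.

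**Conclusion.** The point holds as a mismatch between the SMS adverse event item, the definition of an adverse event, and the follow-up sentence that relies on the SMS. Its main consequence is under-collection of adverse events, chiefly non-serious ones that participants ascribe to existing illness, and the loss of the follow-up contact for them. The amount cannot be derived from the documents.

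Any effect on the go/amend/stop decision is conditional. It needs an event that is serious, truly related, not linked to the programme by the participant, and missed by every other route. If that happens, the row is too favourable. A general claim of bias in the safety row is not supported.

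Severity is minor to moderate. This rests on the article's description of the SMS being a fair account of its text, and on the PHCP record and the visits at 4 and 8 weeks being taken without a relatedness limit, as the article implies.

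**What to change.** Reword the SMS adverse event item to ask about any new or worse health problem or undesirable experience since the last message, with no reference to cause. Judge relatedness afterwards, as a step separate from collection, with the participant's own view as one input. This brings the item into line with the definition and lets the SMS do what the follow-up sentence expects. If the SMS already asks the broader question, correcting the sentence in the Adverse events section is enough.

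The cost is a change of message wording and some additional follow-up calls about complaints that turn out to be unrelated. The sample size, the visit schedule and the Table 2 criteria do not change.

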### Qualitative evaluation

After their last session, participants and PHCPs will be interviewed by a researcher with relevant qualitative expertise to explore the feasibility of the exercise program and barriers and facilitators to their participation.

#### Participant interviews

At the end of the study period, participants will be invited to take part in a one-on-one semi-structured interview to discuss the acceptability of the exercise program, fidelity of delivery, and the barriers and facilitators to adherence with the exercise program. Arrangements for the interview will be made at the time of the last exercise program session (8 weeks), with interviews carried out by a researcher who did not work with the delivery of the exercise program.

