Exercise has been shown to be beneficial for a wide range of conditions that are associated with ageing such as falls [16], frailty [17], and sarcopaenia [18], as well as comorbidities that co-occur with low back pain [19]. Yet, randomised controlled trials of exercise programs for acute and chronic low back pain often do not include older adults with comorbid conditions [20, 21].

Recently, a comorbidity-adapted exercise intervention was designed and tested for patients with knee osteoarthritis [22], showing that tailored exercise therapy provided significant improvements in pain and physical functioning, and that these improvements were of clinical relevance [23]. It is currently unknown whether an exercise program for older adults with low back pain, tailored for the presence of comorbidities, is acceptable for participants and primary healthcare providers (PHCPs) such as physiotherapists and chiropractors. Therefore, this mixed-methods study will assess the feasibility of a comorbidity-adapted exercise program for older people with back pain and comorbidities. Specific aims directly related to assessing the feasibility are as follows:Determine the ability to recruit eligible older participants and report the retention rate.Evaluate adherence to, and fidelity of, the comorbidity-adapted exercise intervention.Assess the collection and completion of outcome measure data, as well as report adverse events.Evaluate the acceptability of the exercise program to participants and PHCPs.

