### Data collection

Data will be collected in person by the research assistant at baseline, 4 weeks, and at 8 weeks after the first exercise program session. Patient demographics and outcome measurement data will be collected in the REDCap — Research Electronic Data Capture system and exported to an Excel spreadsheet. De-identified data will then be imported to STATA/IC® (StataCorp, Texas) for analysis. Qualitative interviews will be performed at 8 weeks, and interview data will be stored securely and transcribed verbatim.

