#### Patient recruitment, retention, and intervention adherence

This study will determine how long it takes to recruit 24 participants, report how many older adults are screened, and how many meet eligibility criteria. Attendance will be recorded at each exercise session, by the PHCP. If a participant fails to attend an exercise session, the research assistant will contact the participant to record a reason for not attending the session and discuss additional support to attend future sessions to prevent dropout. Study retention rates will report the percentage of participants who complete the 8-week exercise program and provide complete data through follow-up. Data on adherence will be collected using a smartphone application. On completion of each exercise session, participants will scan a unique RedCap-generated QR code that will open a brief survey that will document the completion of the exercise session, completion of each component of the exercise session, and provide feedback on their exercise session adherence.

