### Participant withdrawal

Participation is voluntary, and withdrawal from the study at any stage is at the discretion of the participant, and relationships with the study’s researchers, PHCPs, or Macquarie University will not be affected. The research assistant will notify the chief investigator if a participant wishes to withdraw from the trial, and the participant will be asked to complete and sign a withdrawal form. Providing reasoning for withdrawal is voluntary and will be documented. Participants will still be provided with their usual care from their general practitioner if they wish to withdraw from the study.

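### Participant interviews, the main evidence on acceptability under the fourth aim, are arranged at the 8-week last session, and no route is stated for interviewing those who stop early

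*Protocol article*

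**What the plan says.** The Background lists four feasibility aims. The fourth is: "Evaluate the acceptability of the exercise program to participants and PHCPs". Three sections of the Methods set the timing of the participant interview that serves it.

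- Data collection: "Qualitative interviews will be performed at 8 weeks".
- Qualitative evaluation: "After their last session, participants and PHCPs will be interviewed by a researcher with relevant qualitative expertise".
- Participant interviews: "At the end of the study period, participants will be invited to take part in a one-on-one semi-structured interview", followed by "Arrangements for the interview will be made at the time of the last exercise program session (8 weeks".

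The interview is to cover acceptability, fidelity, and what helps or hinders adherence. The Analysis section codes the interview transcripts to the Theoretical Domains Framework to draw out acceptability, barriers and facilitators, and continues coding until saturation.

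For people who miss sessions or leave, the protocol has two contacts. After a missed session "the research assistant will contact the participant to record a reason for not attending the session" and to discuss support for coming back. At withdrawal the participant completes a form, and "Providing reasoning for withdrawal is voluntary and will be documented". Neither contact is linked to an interview.

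**The concern.** The chance of being interviewed depends on the thing being studied. People who found the program unacceptable, or met a barrier they could not overcome, are the least likely to be present at the last session in week 8. If the plan is followed as worded, the participant transcripts answer mainly how acceptable the program was to those who stayed. Coding to saturation does not help: saturation among finishers shows that finishers have no new themes, not that stoppers have none.

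This matters for the decision that the study feeds. In Table 2 amber means that there are remediable problems to amend before proceeding with caution. The accounts of people who stopped are the most direct evidence of what needs amending, and they are hard to recover later if not sought close to the time of stopping.

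**Working it through.** No estimate in the plan is disputed. The check sets the sections side by side and then bounds the size of the group concerned.

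**1. Sample size (context only).** The Participants section states 24, from a red limit of 0.45, a green limit of 0.75, one-sided alpha 0.05 and beta 0.1. With the usual one-sample formula,

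n = (1.645·√(0.45·0.55) + 1.282·√(0.75·0.25))² / 0.30² = (0.818 + 0.555)² / 0.09 ≈ 20.95.

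With continuity correction, n/4·(1 + √(1 + 2/(n·0.30)))² ≈ 24.17. The stated 24 is therefore close to the corrected value. The point does not depend on it.

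**2. Timing of the interview.**

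| Section | When | Does it reach an early stopper? |
|---|---|---|
| Data collection | 8 weeks | No route stated |
| Qualitative evaluation | After the person's last session | Possibly, if this means the last session attended |
| Participant interviews | Invited at study end, arranged at the last session, given as 8 weeks | Not excluded, but absent when arrangements are made |

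Two of the three sections fix 8 weeks. The third is open to either reading, and it covers participants and providers in one sentence, while provider interviews come at the end of the program. The wording does not settle the matter in favour of early stoppers.

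**3. Other sources that bear on barriers or acceptability.**

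| Source | What it gives | Limit for early stoppers |
|---|---|---|
| Missed-session contact | Reason for absence, support discussed | Not an interview; not named in the Analysis section |
| Survey after each session: "provide feedback on their exercise session adherence" | Components completed, feedback | Opens only when a session has been completed |
| Withdrawal form | Reason, if offered | Voluntary; not named in the Analysis section |
| Satisfaction and perceived effect at 4 weeks | Two ratings | No explanation of why someone stopped |
| Daily SMS | Pain score, undesirable experiences | Does not ask about acceptability |
| Provider interviews and diaries | Barriers as providers see them | Not the participant's own account |

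These sources are real and some reach people before week 8. None is a participant interview on acceptability.

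**4. How large the group could be.** From the retention row of Table 2:

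- Green requires at least 75%: 0.75 × 24 = 18 retained, so up to 24 − 18 = 6 not retained.
- Amber requires at least 50%: 0.50 × 24 = 12 retained, so up to 24 − 12 = 12 not retained.

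The section on recruitment, retention and adherence counts a participant as retained only if the program is completed and complete data are provided. Someone who attended to the end but has missing data is therefore also non-retained. The figures 6 and 12 are upper bounds on early stopping, not forecasts of it.

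**The case against.** The strongest reply has four parts.

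**Interviews are not the sole source.** A reader might infer that acceptability and barriers are explored only through the 8-week interviews. The documents do not support that: the sources tabulated above also contribute, and the provider diaries are reviewed expressly for barriers. This part stands.

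**Early stoppers are not excluded.** A reader might also infer that they are shut out by rule. No section limits the interview to completers, the invitation is addressed to participants without qualification, and the Qualitative evaluation wording may include them. A person who missed the last session might also be seen at the 8-week data collection, which is in person. This stands too: what the article shows is a procedure that does not reach them, not a rule against them.

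**Poor adherence is not dropout.** Table 2 has separate rows for the two. Someone who attends half the sessions or fewer may still be in the study at 8 weeks and be interviewed, so some barriers to adherence would be heard. This narrows the gap but does not close it.

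**An article may leave interview procedures to a fuller document.** This would answer a complaint of mere silence. Here the article does state when interviews take place and when they are arranged, and two of its sections differ in wording. The procedure as stated is what needs changing.

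**Conclusion.** The point holds as a gap in the stated procedure. Following the Data collection and Participant interviews sections, participants who stop early have no stated route into the main participant evidence for the fourth aim. The coded participant themes would then come mainly from those still attending at 8 weeks. Up to 6 of 24 could be non-retained at green and up to 12 of 24 at amber, with early stoppers being some or all of these.

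It is tempting to turn this into a numerical overstatement of acceptability. The documents give no basis for that. The interviews are coded for themes and report no percentage who find the program acceptable, acceptability among stoppers is unknown, and Table 2 has no row for acceptability as judged from the interviews. No progression threshold or sample size is affected.

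The conclusion assumes that no further document gives early stoppers a route, and that the 8-week timing is applied as written. On that basis this is a cheap improvement worth making before interviews begin.

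**What to change.** Reconcile the Data collection, Qualitative evaluation and Participant interviews sections so that every enrolled participant is invited to the interview. For those who stop early, offer it at the existing missed-session or withdrawal contact and hold it by telephone soon afterwards with the same interview guide. Taking part stays voluntary. Report how many stoppers and how many finishers were interviewed, and present their themes separately.

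The cost is a small wording change to the protocol and consent material. It should need no added staff, and the number of participant interviews stays within the 24 participants planned. The downside is small: some stoppers will decline, and interviews will be spread over time instead of falling together at week 8.
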